### Tool adaptation

The tool adaptation process consisted of several steps to ensure it satisfied the variable workflows and clinical content needs of each site.

#### Clinical prediction rules

We focused on respiratory tract infections and chose well-validated CPRs for evaluating the risk of streptococcal pharyngitis (sore throat) and pneumonia (cough). We chose the Centor criteria [10] for adults with sore throat which includes four criteria: absence of cough, pharyngeal exudates, tender anterior cervical lymphadenopathy, and fever. We chose the McIssac criteria [13] for children with sore throat which mirrors Centor criteria with the addition of patient age. We chose the Heckerling criteria [12] for adults with risk of pneumonia which include five criteria: fever, increased heart rate, crackles, decreased breath sounds, and absence of asthma (Table 3).

**Table 3 Tab3:** Clinical prediction rules for strep pharyngitis and pneumonia

Strep pharyngitis			Pneumonia
	Children	Adults	Adults
Age range	3–17 years old	18–70 years old	18–70 years old
Rule	McIsaac [13]	Centor [10]	Heckerling [12]
Criteria	Tonsillar exudate +1 Tender anterior cervical adenopathy +1 Lack of cough +1 History of fever +1 3–14 years old +1	Tonsillar exudate +1 Tender anterior cervical adenopathy +1 Lack of cough +1 History of fever +1	Temperature > 100 F +1 HR > 100 bpm +1 Crackles (rales) +1 Decreased breath sounds +1 Absence of asthma +1

*HR* heart rate, *bpm* beats per minute

#### Comparing workflows

The current iCPR tool is adapted from the previous iCPR tool but tailored to fit the current sites’ unique workflows. The iCPR tool design was developed by an interdisciplinary team of experts in primary care, usability, and clinical informatics. Interviews were held with providers, clinic managers, and medical assistants at each site to determine general clinic workflows as well as specific workflows for rapid strep and chest x-ray testing.

These interviews demonstrated that workflows varied dramatically by institution with some variation by clinic and even by provider within a clinic. For example, a major difference between institutions was that University of Utah providers heavily leveraged an EHR-assisted documentation pathway called “NoteWriter.” This structured documentation template has the ability to create pick-list histories based on the patient’s chief complaint. In this workflow, medical assistants record a structured history that the provider then reviews and confirms with the patient. The structured history, as well as the vital signs and, if used, structured physical exam then populates the iCPR tool. This decreases the need for duplicate documentation. Another workflow difference was a variable approach among clinics to rapid strep testing including which clinic personnel review test results and whether patients remain in the clinic until results are complete.

#### Updating clinical content

The clinical content of the iCPR order sets and the underlying triggering logic required review and revision to meet current national and local standards of care. An interdisciplinary team of experts in primary care, infectious disease, laboratory medicine, and clinical informatics met to determine appropriate medical care for patients with sore throat and cough for varying disease risk levels. National guideline recommendations, clinical studies, and local antibiotic resistance and practice patterns guided the group’s choices regarding the iCPR tool content. For example, first-line antibiotic choices for pneumonia were based on the Infectious Disease Society of America’s guideline [14] but tailored to local strep pneumonia resistance patterns.

### Tool design considerations

The team also reviewed all of the iCPR tool features and designs to ensure it met the needs of the diverse clinics. This included examining the (1) tool activation level, (2) timing of alerts, (3) integration into clinical workflow, (4) alert triggers, and (5) interruptive versus non-interruptive alerts.Tool activation: We chose to activate the tool based on the clinic where the encounter was performed instead of at the provider level. The clinic was chosen to coincide with the unit of randomization and to prevent study contamination from providers that worked at multiple clinics.Timing of alerts: It was clear from interviews with providers that there was variation in when they ordered tests and antibiotics during the patient encounter. We chose to base the main trigger on the reason for visit despite infrequent completion of this field by providers in the original iCPR clinical site [9]. Relying on reason for visit as the main trigger made iCPR available early in the encounter and throughout the subsequent workflow. We also included a secondary trigger, similar to the original iCPR design, that would occur toward the end of the encounter based on diagnosis and a combination of diagnosis and orders. While the secondary trigger may not be frequently used, it might allow providers to change decisions or at least alert them to considerations for future encounters. We also automatically triggered alerts in the provider’s inbox and when the provider reopened an encounter after a relevent test had resulted.Integration into clinical workflow: The iCPR needed to be integrated into active clinical practice without disrupting patient care. It is clear that without integration into workflow, CDS tools are not used [15]. This led to some individualization between institutions including the use of NoteWriter at some sites. We also decided to make iCPR as flexible as possible in order to facilitate the integration into various workflows. This included the ability for providers and nurses to use bundled ordersets based on test results and for support of telephone encounters or patient portal encounters.Alert triggers: Another guiding principle was limiting the number of inappropriate triggers. We balanced trigger sensitivity and specificity, erring on the side of specificity at the cost of missing some potentially appropriate encounters. Triggers were determined by reviewing clinic data from the previous year for the final encounter diagnoses based on available reasons for visit and whether antibiotics were prescribed. We found that only three reasons for visit commonly resulted in diagnoses that we wanted to affect. Based on these, we chose “cough/chest congestion,” “URI (upper respiratory infection),” and “sore throat” as the reason for visit triggers. For triggers based on diagnosis and antibiotics, we chose the narrowest diagnoses and only antibiotics commonly used in respiratory infections (Table 2).Interruptive vs non-interruptive alerts: Interruptive alerts interfere with workflow and force users to acknowledge the alert, potentially increasing clinician frustration and alert fatigue [16, 17]. Given the broad nature of the three reasons for visit triggers we chose, we knew that iCPR was likely to trigger at times when it would not be helpful, such as when a patient with asthma or sinusitis presented with a cough. Based on the risk of inappropriate triggers as well as provider opinions from the interviews, we chose to use non-interruptive alerts for the reason for visit triggers. We explored options for non-interruptive alerts for the diagnosis triggers, but there were no mechanisms within the EHR that allowed us to do this. Thus, we opted for interruptive alerts if iCPR was triggered by a diagnosis or diagnosis plus antibiotic prescription.

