### Randomization

A computer-generated, blocked, stratified-randomization scheme was performed at the level of the clinic. Stratification was by institution and by the number of patient visits to the clinic in the previous year that would have triggered the iCPR tool. Three strata of visits were used: <750, 750–1500, and >1500. Group assignment was performed by the study statistician.

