### Intervention and control groups

Both groups received a 45-min academic detailing session that included a review of the CPRs used in the study, discussion of evidence-based diagnosis of strep pharyngitis and pneumonia, and guidelines for treating strep pharyngitis and pneumonia. Participants were given handouts with the CPRs and treatment guidelines and links to online resources. Academic detailing sessions at intervention clinics also included an overview of the iCPR tool with a live demonstration in the EHR. Participants received handouts about iCPR and links to additional online training materials. Providers that were unable to attend the academic detailing were given access to printed and online training materials. The iCPR tools were made active in the EHR for providers at intervention clinics on the day of the academic detailing, thus giving providers immediate access. Control groups did not receive access to the iCPR tools.

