#### “Near live”

The goal of the near live testing was to determine how the tool fits with providers’ workflows. Eight primary care providers from the University of Wisconsin were selected from volunteers. Inclusion criteria were similar to those used in the think aloud testing. In a clinic office setting, each participant interacted with a simulated patient, an actor who was trained to portray a case of low-, intermediate-, or high-risk strep pharyngitis or pneumonia. The participant interacted with the patient actor while navigating through the CDS tool. Participants were told to think out loud if they had any challenges or positive experiences with the tool. The study staff observed the sessions to answer questions, troubleshoot the software, and provide the physical exam information. After completing the testing, participants were asked about their reaction to specific components of the tool and for suggestions for improvement. Every participant completed at least one case, and two completed two cases each. The duration of each session was between 25–45 min. Two independent coders reviewed all recorded screen captures and the transcribed audio. Verbalized thoughts and participant actions were coded. Based on usability testing, multiple modifications were made to the wording and format of the alerts, calculators, and smart sets. Also, specific ranges of risk were included in the calculator and some non-antibiotic medication orders were removed from the smart sets.

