#### Clinical practice outcomes

The study outcomes were designed to evaluate changes in clinical practice related to iCPR tool use. The primary outcome is the difference in antibiotic prescribing rates in iCPR patient encounters in intervention versus control providers. Secondary outcomes include the rates of rapid strep, throat culture, and chest x-ray ordering and the class of antibiotics prescribed. To measure the safety of clinical care, we will evaluate rates of additional encounters to primary care or urgent care, hospitalization, and prescription of respiratory tract antibiotics within 1 week of the index encounter.

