### Statistical analysis

Planned statistical analyses include comparison of patient and provider characteristics between groups to evaluate for group balance. Descriptive statistics will be used to show the use of iCPR components in the intervention group. A three-level logistic regression model with a random effect for practice and one for provider within practice will be used to assess the primary outcome and other clinical outcomes. A fixed effect will be included for intervention and for randomization strata. Subgroup analysis by primary institution (Wisconsin or Utah) and provider training will be performed. An interim analysis will be done 1 year after the last clinic receives academic detailing. Comparison of iCPR component use based on provider training and gender will be performed using a three-level logistic regression model with a random effect for practice and for provider within practice with fixed effects for provider training and gender.

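### Providers who work at several clinics do not fit the nested provider effect or the provider-worded primary contrast, and activating the tool by clinic limits contamination without preventing it

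*Protocol article*

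**What the plan says.** Protocol article, Randomization: "A computer-generated, blocked, stratified-randomization scheme was performed at the level of the clinic". Tool design considerations: "We chose to activate the tool based on the clinic where the encounter was performed instead of at the provider level", with the reason "The clinic was chosen to coincide with the unit of randomization and to prevent study contamination from providers that worked at multiple clinics". That reason takes it as given that some providers work at more than one clinic.

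Intervention and control groups: both arms receive the detailing session and handouts on the prediction rules. Only the intervention arm gets tool training: "Academic detailing sessions at intervention clinics also included an overview of the iCPR tool with a live demonstration in the EHR". Control clinics have no access to the tool.

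Clinical practice outcomes: the primary outcome is the difference in antibiotic prescribing rates in "iCPR patient encounters in intervention versus control providers".

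Statistical analysis: a three-level logistic model "with a random effect for practice and one for provider within practice", with fixed effects for intervention and randomization strata.

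Clinical data collection: clinic site is recorded for each encounter.

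**The concern.** Three statements do not sit together once a provider can appear at two clinics.

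- **The safeguard.** Activation by clinic governs where the tool fires. It does not govern what a provider has learned from it elsewhere. Carry-over into control encounters would pull the observed difference towards zero.
- **The primary contrast.** Arm is attached to the provider in the outcome wording but to the clinic in the randomization and in the activation rule. For a provider with clinics in both arms the outcome wording gives no answer.
- **The model.** Strict nesting treats the same person at two clinics as two unrelated people. The covariance left out can make the standard error of the treatment effect too small or too large, depending on whether the two clinics share an arm.

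At stake are a primary contrast with one clear meaning, a correct standard error, and the reading of a small or null result.

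**Working it through.** The article gives no figure for the number of multi-clinic providers or for carry-over, so there is no plan figure to reproduce on this point. What follows is a range under stated assumptions.

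**Inputs from the article.** Table 1: 22 + 11 = 33 clinics; 12 + 6 = 18 intervention, hence 15 control; 268 + 111 = 379 providers. Power calculation: 52,457 encounters (used here only as a volume), clinic ICC 0.01–0.05, effect 10 points.

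**Assumed.** 10–30% of providers work at two clinics and split their encounters equally. The provider ICC is 0.05–0.10.

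**Standard error: method.** Work on the risk scale in units of p(1 − p), with one cell per provider-clinic pair. Let ρc and ρp be the clinic and provider ICCs. Two cells of one provider truly have covariance ρp; the nested model sets it to 0. The omitted term in the variance of the arm difference is +2w²ρp for each pair in the same arm and −2w²ρp for each pair in opposite arms, where w is the cell weight.

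**Hand check, upper end** (30% at two clinics, ρc = 0.01, ρp = 0.10):
- Two-clinic providers: 0.30 × 379 ≈ 114. Cells: 265 + 228 = 493, or 246.5 per arm, weighted about equally because provider variance dominates.
- Encounters per provider: 52,457/379 ≈ 138. Residual variance: 0.89/138 ≈ 0.0064 for a full cell and 0.0129 for a half cell, average about 0.0094.
- Nested variance: 2 × 0.01/16.5 + 2 × (0.10 + 0.0094)/246.5 = 0.00121 + 0.00089 = 0.00210.
- Omitted term: 2 × 114 × 0.10/246.5² = 0.000375.
- All pairs in the same arm: √(0.00210/0.002475) = 0.92, so the nested SE is about 8% too small.
- All pairs in opposite arms: √(0.00210/0.001725) = 1.10, so the nested SE is about 10% too large.

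**Hand check, lower end** (10%, ρc = 0.05, ρp = 0.05):
- 38 two-clinic providers; 341 + 76 = 417 cells, 208.5 per arm; average residual about 0.0077.
- Nested variance: 2 × 0.05/16.5 + 2 × (0.05 + 0.0077)/208.5 = 0.00606 + 0.00055 = 0.00661.
- Omitted term: 2 × 38 × 0.05/208.5² = 0.000087.
- The resulting error is about 0.7% in either direction.

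**Random second clinics.** The chance that two clinics drawn at random are in opposite arms is 2 × 18 × 15/(33 × 32) = 0.51, so the positive and negative terms nearly cancel.

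**Full generalized least squares** with 18 and 15 clinics refines these figures:

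| Second clinics | Nested SE against its true SE |
|---|---|
| Random | within about 0.5% |
| All in same arm | about 0.5–7% too small |
| All in opposite arm | about 0.6–9% too large |

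A crossed provider effect reduces the true SE by about 0.3–13% over the same grid.

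**Dilution.** Observed difference = 10 × (1 − s × c), where s is the share of control encounters handled by cross-arm providers and c is the fraction of the effect they carry over (both assumed).
- s = 10%, c = 50%: 10 × (1 − 0.05) = 9.5 points.
- s = 20%, c = 100%: 10 × (1 − 0.20) = 8.0 points.
- Wider range, s = 5–30% and c = 25–100%: 9.9 down to 7.0 points.

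This formula weights all control encounters alike. A crossed model also draws on each cross-arm provider's own contrast, which under carry-over is 10 × (1 − c). Its estimate can therefore be diluted more than the formula shows.

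**The case against.** **The safeguard does what was meant.** The choice was between activation by provider and by clinic. Activation by provider would have fired the tool in control-clinic encounters; activation by clinic does not. This stands, and it is why the correction is from *prevent* to *limit*. A reader might infer that the safeguard fails or that contamination is established. The article supports neither. It gives no count of multi-clinic providers and does not say that any of them cross arms, and those who stay within one arm contaminate nothing. Both arms are taught the rules, so only tool-specific experience can carry over, and high values of c are upper bounds. The remark about later encounters, "it might allow providers to change decisions or at least alert them to considerations for future encounters", concerns only the secondary trigger, which the article expects may be little used.

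**Arm is already implied by clinic.** Randomization, activation and data capture all run by clinic, and the abstract compares groups. This is fair: the outcome wording is probably loose and not a different design. It is still the definition of the primary outcome, and it is the one place that attaches arm to the provider.

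**Nesting has no practical effect.** This is true when second clinics are random with respect to arm. It does not hold when they cluster in the same arm or in opposite arms, and the article does not say which applies.

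**These are details for the analysis plan.** Many are. The nested effect and the provider-worded contrast, however, are stated in the article and do not fit the data structure that it acknowledges.

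**Usability testers.** A reader might count them as a further source of contamination, since ten providers took part in think-aloud testing and, for the near-live round, "Eight primary care providers from the University of Wisconsin were selected from volunteers". The article does not say that they practised at study clinics, still less at control clinics. Eligibility extended to urgent care, and each session lasted 25–45 minutes on simulated cases. This is speculation and not part of the point.

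**Conclusion.** The point holds as a mismatch between the acknowledged data structure and two stated analysis choices, together with one word that claims too much. The effect on the standard error runs from negligible to about 7% too small or 9% too large. That rests on the assumed 10–30% of providers at two clinics, equal splitting of encounters, clinic ICC 0.01–0.05 and provider ICC 0.05–0.10. Dilution is towards no effect; its size depends on two quantities that the article does not give.

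A reader might go further and say that contamination strikes a trial already below 80% power. The article does not support that as a general statement. Taking 52,457 encounters over 33 clinics and 40% against 30%, approximate two-sided power is 0.765 at ICC 0.05. At ICC 0.01 it stays at 0.98 or above even under the widest dilution range shown. The shortfall belongs to the top of the ICC range and is a separate matter.

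**What to change.** 1. **Clinical practice outcomes:** define arm by the clinic of the encounter, and replace the comparison of providers with one of clinics.
2. **Statistical analysis:** use one identifier per provider across all clinics, with a provider random effect crossed with practice.
3. **Reporting:** give the number of providers and encounters that cross arms.
4. **Sensitivity analysis:** exclude cross-arm providers' encounters from both arms. It is needed because the crossed model uses within-provider contrasts, which carry-over would dilute. Dropping them from the control arm alone would unbalance the randomized comparison.
5. **Tool design considerations:** write *limit* in place of *prevent*.

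The cost is small. The stated model already needs clinic and provider for every encounter, so no new data and no design change are required. The downside is slightly more analysis work and fewer encounters in the sensitivity analysis.

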
### iCPR components

iCPR is triggered when a matching reason for visit, diagnosis, or diagnosis plus antibiotic order is entered (Table 2). This initiates an alert to the provider that decision making regarding diagnostic and treatment options for the patient might be assisted by the use of iCPR. Providers can then choose to click on a link and go to the risk calculator. Once the risk calculator is completed, another alert provides a link to access bundled order sets that include orders, documentation, diagnosis, and patient education materials (Fig. 1).

**Fig. 1 Fig1:**
[figure not shown]
iCPR work flow. *MA* medical assistant, *RFV* reason for visit, *BPA* best practice alert

#### Alerts

At the University of Wisconsin, a standard EPIC alert is used to inform providers when a patient is appropriate for iCPR. Providers are familiar with seeing these alerts for other conditions. The alert specifies why iCPR was triggered and includes a link to the risk calculator. In addition to this alert, the University of Utah placed an additional tab in NoteWriter. This tab, called “Provider Score,” was populated with the appropriate iCPR criteria (Centor, McIsaac, and/or Heckerling) based on the reason for visit. In all other cases, it was blank. The Provider Score tab of NoteWriter draws information from vital signs and structured history and physical exam documentation. It can also be completed ad hoc. After completion, the score and interpretation are visible to the provider. The calculator score also drops directly into the clinical note.

#### Risk calculators

We chose documentation flow sheets for the calculator to allow calculation of risk scores based on CPR criteria (Fig. 2). All calculators use simple yes/no buttons for choosing if the criteria were met. The age in the McIssac criteria is automatically entered from the birthdate in the EHR, and the heart rate and temperature are automatically entered in the Heckerling criteria from the current encounter vitals. Calculators display a risk score from 1–5 and the range (low, intermediate and high) of risk of strep pharyngitis or pneumonia based on results from previous validity studies [18, 19].

